### Sample size

This study aims to recruit 120 participants. In 2014, Christchurch New Zealand had 6575 live births [136]. Assuming at least 12% of pregnant women meet criteria for depression / anxiety and accounting for 1 in every 100 pregnancies being twin births, approximately 781 women per year would be eligible for the proposed study in Christchurch alone. A placebo-controlled RCT providing multinutrient supplementation to adults with ADHD [73] showed a between groups effect size of 0.64 on a measure of depression. Other RCTs found a between groups effect size of 0.39 on the EPDS when comparing a multinutrient supplement with a placebo in healthy postnatal women [137] and an effect size of 0.88 on depression outcomes from use of a B vitamin complex compared with placebo for participants with major depressive disorder [138]. Based on these findings, to detect a medium to large effect (0.6) using a two-tailed significance level of 0.05 and a power of 0.8, 45 participants per group would be needed. Assuming an attrition rate of 30% based on the mean dropout rate from the pregnant and postnatal population, 60 participants per group would provide optimal power.

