### Data analysis

Demographic characteristics will be compared across the treatment groups using independent samples *t*-tests in order to test for potential failures of randomization.

For the primary outcomes (EPDS and CGI-I scores), the repeated measures of the outcome variables will be modelled using generalized linear mixed effects regression models using Stata 15 [140]. These models will permit the testing of differences between the multinutrient group and the active control group over the course of the trial. In the case of the EPDS, baseline scores will be used as a covariate factor. For secondary outcomes (e.g. MADRS, DASS), linear mixed effects models will also be used.

The pooled mean scores (and standard deviations) over the course of the trial on each of the primary outcomes will be used to compute estimates of effect size (Cohen’s *d*). Clinical significance between groups will be identified by a minimum of a three point difference in EPDS scores. Clinical significance within groups will be identified by a four point change on the EPDS as described by Matthey [141]. A clinical significant change will be categorised as the following: ‘Recovered’: participants who move from a score of 13 or more at baseline to 11 or less following treatment and whose score has reduced by four points; ‘Improved’: participants whose baseline score reduces by four points post treatment but is still above 13 or more; ‘Deteriorated’: participants whose baseline score increases by four points post treatment; ‘No change’: participants whose pre-post score is less than a four point change.

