All data will be analysed on an intention-to-treat basis using the last observation carried forward method and as such will include all participants’ data regardless of treatment compliance. Treatment adherence will be measured by the total number of capsules consumed throughout the trial phases. Only participants who consume 70% or more of the total number of capsules will be considered adherent to the treatment. A per-protocol analysis, which excludes participants with protocol violations (e.g. drop out, non-adherence to treatment consumption) will be performed on the primary outcomes (EPDS and CGI-I) in order to compare differences in treatments responses between participants who were adherent with the treatment and those who discontinued participation or were non-adherent. Outcomes from the open label phase will be compared to the group outcomes from the week 12 observation of the RCT phase using generalised linear mixed effects regression models taking into account participants self-reported use of micronutrients.

To assess the effect of the multinutrient intervention has on infant development, we will compare those infants exposed to the multinutrients versus those infants not exposed to the multinutrients on emotional, cognitive and physical development. Length of exposure to the multinutrients (due to the RCT phase and varying starting points during gestation) and score on the EPDS will also be considered as continuous variables in considering infant outcomes. Hierarchical regression analysis will be run using Stata 15 in order to identify if perinatal/postpartum depression and multinutrient exposure are predictors of improved self-regulation of the infant across the various time points. Descriptive statistics for each participant will be used to compare demographic characteristics between the treatment groups to allow any differences to be controlled.

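### The per-protocol analysis excludes drop-outs and non-adherent women, yet its stated purpose is to compare adherent women with them

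*Protocol article*

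**What the plan says.** All statements are in the protocol article, under Data analysis unless noted.

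- The randomised contrast: "These models will permit the testing of differences between the multinutrient group and the active control group over the course of the trial". The Abstract places this comparison on an intent-to-treat basis.
- The main analysis set "will include all participants’ data regardless of treatment compliance".
- The adherence threshold: "Only participants who consume 70% or more of the total number of capsules will be considered adherent to the treatment". The sentence before it counts capsules over the trial's phases, in the plural.
- The per-protocol set: "A per-protocol analysis, which excludes participants with protocol violations (e.g. drop out, non-adherence to treatment consumption) will be performed on the primary outcomes", namely EPDS and CGI-I.
- The purpose, in the same sentence: "in order to compare differences in treatments responses between participants who were adherent with the treatment and those who discontinued participation or were non-adherent".

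Two other sections bear on who discontinues. Under Intervention, women who are prescribed and take psychiatric medication are withdrawn. Under Safety monitoring and reporting, a woman whose symptoms worsen in the RCT phase may be offered the open-label product early, and one who deteriorates to a clinically significant degree may be withdrawn.

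**The concern.** One sentence sets an exclusion rule and a purpose that cannot both be met. An analyst who applies the rule has no discontinued or non-adherent women left to compare. An analyst who follows the purpose has to bring those women back and compare groups defined by what happened after randomisation. The two analyses answer different questions, and either could be reported as the per-protocol result on both primary outcomes.

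The second analysis loses the protection of randomisation. The protocol's own withdrawal provisions direct women who are doing badly, in either arm, towards the discontinued group. Adherent women may therefore look better whatever the capsules contain.

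**Working it through.** **1. Rule against purpose**

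| Element of the sentence | Women involved |
|---|---|
| Excluded from the analysis | Drop-outs; non-adherent women |
| First comparison group | Adherent women |
| Second comparison group | Women who discontinued or were non-adherent |

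The second comparison group and the exclusion list name the same women. After exclusion that group is empty. No other part of the article describes a separate adherence analysis, or says that the per-protocol result is to be set beside the intention-to-treat result as a sensitivity analysis.

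**2. The plan's own figure, for scale**

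The Sample size section gives the requirement as follows: "to detect a medium to large effect (0.6) using a two-tailed significance level of 0.05 and a power of 0.8, 45 participants per group".

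- Normal approximation: n = 2(1.960 + 0.842)² / 0.6² = 43.6, so 44 per group.
- Two-sample t-test: 44.6, so 45 per group. The stated figure reproduces.

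**3. What the purpose clause could show under no treatment effect (illustration)**

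Inputs:

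- Proportion non-adherent: 0.30. This borrows the 30% attrition assumption in Sample size. Attrition is only a proxy, because a woman who completes can still fall below 70% of capsules.
- Correlation r between a normally distributed adherence propensity and prognosis: 0.2, 0.3 and 0.4. These are assumed; the article gives no value.

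The cut that leaves 30% below it has normal density 0.3477. The difference in mean propensity between adherent and non-adherent women is

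0.3477/0.7 + 0.3477/0.3 = 0.497 + 1.159 = 1.656 SD.

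Multiplying by r gives the difference in outcome when the formula does nothing:

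| Assumed r | Spurious difference (SD) |
|---|---|
| 0.2 | 1.656 × 0.2 = 0.33 |
| 0.3 | 1.656 × 0.3 = 0.50 |
| 0.4 | 1.656 × 0.4 = 0.66 |

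A simulation with one million draws gave 0.33 at r = 0.2 and 0.49 at r = 0.3, in agreement. At r = 0 the difference is zero.

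**4. What the randomised contrast within adherent women would offer**

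If 30% drop out, 60 × 0.7 = 42 per arm remain. Power for an effect of 0.6 is then about 78% (t-test). If a further 10% or 20% of completers (assumed) fall below 70% of capsules, it is about 73% or 68%. That is adequate for a supportive analysis.

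**The case against.** The strongest reply is that this is loose drafting. The sentence comes shortly after the intention-to-treat statement. The likeliest intent is an ordinary per-protocol comparison of the two arms, set beside intention-to-treat to see how the result changes when non-adherent women are left out. On that reading no adherent-versus-non-adherent test is planned. The intent is plausible, but the text does not say it; it names a different contrast. A fuller analysis plan could not simply add detail, because it would have to overrule one half of the sentence.

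Three stronger readings are tempting and are not supported:

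- A reader might infer that the trial's efficacy conclusion is at risk. It is not: efficacy rests on multinutrient versus active control by intention to treat, and nothing in the article makes a claim depend on the per-protocol result. Describing outcomes by adherence is not an error in itself; reading the difference as a treatment effect would be.
- A reader might infer that drop-outs' outcomes in such a contrast would come from last observation carried forward. The article ties that method to the intention-to-treat analysis and does not say how it would apply here.
- A reader might treat 0.33 to 0.66 SD, or a false-positive rate computed from it, as a measured bias. The correlations are assumed, dropout stands in for non-adherence, and the article does not say that the arms would be pooled. Adjustment for baseline EPDS would also remove part of any prognostic difference on that outcome.

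It is also fair to say that multinutrient versus control among adherent women is selected after randomisation. The recommended analysis is therefore supportive only.

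**Conclusion.** The point holds as an internal contradiction in a stated analysis of both primary outcomes. The exclusion rule makes the stated comparison impossible, and the stated purpose, if followed, gives a non-randomised contrast. This conclusion needs only the one sentence and the definition of adherence; it does not depend on any calculation.

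The range of 0.33 to 0.66 SD shows that, under moderate assumed correlations, such a contrast could be of the same order as the planned effect of 0.6 with no treatment effect at all. It is an illustration and not an estimate for this trial.

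The reach is limited. The analysis is supplementary and the intention-to-treat result stands. The sentence should still be corrected, because otherwise the choice between two different analyses under one label could be made after the data are seen.

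**What to change.** Replace the sentence so that it states:

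- **Contrast:** multinutrient versus active control, on EPDS and CGI-I, with the same model as the primary analysis.
- **Set:** women who took at least 70% of the capsules due in the RCT phase. The present count runs over the trial's phases, so capsules taken in the open-label phase, when every participant is offered the multinutrient, could decide who enters an RCT-phase comparison.
- **Status:** supportive of intention-to-treat, with a note that the set is formed after randomisation and is itself open to selection.

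Drop the comparison of adherent women with discontinued or non-adherent women. If it is wanted, list it separately as descriptive and observational, with no inference about treatment effect.

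The cost is a few lines of wording, fixed before unblinding. No new data, visits or participants are needed.

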## Methods/design

### Trial design

This randomized, double-blind, controlled trial is designed to compare the efficacy and safety of a broad-spectrum multinutrient formula to an active control formula for the treatment of depressive and anxiety symptoms in pregnant women, allocated in a 1:1 ratio. The 12 week RCT phase of the trial will be followed by an open label phase where participants can take the multinutrient intervention until the birth of their infant. The open label phase was included in order to provide participants with the opportunity to try the nutrients regardless of the random allocation in the RCT phase without breaking the blind. Participants will be followed up naturalistically until 12 months postpartum.

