### Eligibility criteria

Pregnant women who are between 12 and 24 weeks gestation will be recruited and followed throughout their pregnancy until 12 months postpartum. The inclusion criteria are aged ≥16 years; low risk singleton pregnancy; free from psychiatric medication for 4 weeks; score of ≥13 on the Edinburgh Postnatal Depression Scale (EPDS) during their second trimester and deemed reliable and compliant with the protocol. The exclusion criteria include regular vomiting; current/recent significant pregnancy complications (e.g. placenta praevia, preeclampsia, gestational diabetes), known foetal abnormalities; serious current or historical medical condition (e.g. hypertension, kidney disease); known allergy to the ingredients of the intervention; known metabolic condition (e.g. Wilson’s disease, hemochromatosis); untreated or unstable thyroid disease; known neurological disorder (e.g. epilepsy, multiple sclerosis, narcolepsy); desire to continue taking prenatal supplements that either exceed the upper limit or are not required for medical purposes (decisions discussed and made on a case-by-case basis).

All participants will be invited to enrol their infant in the study examining infant development over the first 12 months of life.

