**Active Control Supplement Facts**	
Amount per serving (12 capsules)	
Riboflavin	1.2 mg
Potassium Iodide	150 mcg
Silicon dioxide	30 mg
Magnesium stearate	60 mg
Microcrystalline cellulose	6 g

DEN was chosen for this study as the combination of nutrients it contains is the most studied combination in the world for the treatment of psychiatric illnesses [51] and has found robust effects on a range of psychological symptoms that are also implicated in antenatal depression and anxiety [52, 69–72]. Furthermore, the safety and tolerability of this combination of multinutrients is well documented in both adults and children [72, 73].

During the RCT phase of the trial, participants will be able to continue taking omega 3 and probiotic supplements if they were taking these prior to screening for the trial. Participants will also be able take iron, if needed, at any time during the pregnancy and will be able to continue any form of psychotherapy that had begun prior to screening. Participants will be withdrawn from the study if they are prescribed and take any psychiatric medication given the potential interaction with nutrients. Participants will be encouraged before enrolment in the trial to avoid taking additional nutrients, other than those needed for medical reasons, throughout the duration of the trial in order to minimize the risk of adverse events. However, they may be withdrawn from the trial if the dose of a prescribed vitamin or mineral supplement exceeds the upper limit. Decisions on continued participation in the trial will be made on a case-by-case basis. The upper limit is the maximum dose of a nutrient that can be taken without any adverse effects.

Following the 12-week RCT period, all participants will be invited to enter an open label phase until the birth of their infants and where the capsule dose will be identical and follow the same titration procedure as the RCT phase. The product is commercially available for participants to purchase should they wish to continue taking the multinutrients post-trial.

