### Safety monitoring and reporting

A protocol is in place to respond to situations in which a participant reports adverse symptoms of either a physical or psychological nature throughout the duration of the trial. Adverse events and side effects will be monitored within the first week of the trial via telephone and fortnightly thereafter via a questionnaire asking participants to identify any new medical problems, infections, hospitalizations (excluding birth) and medication and supplement use. Participants will be advised to contact the study investigators if they are concerned about any increases in physical or psychological symptoms.

Should a participant’s psychological symptoms worsen, they will be instructed to contact the study investigators who in discussion with the participant, may refer them to their General Practitioner (GP), psychiatric emergency services or may decide to offer the open label option earlier if there is a worsening in symptoms during the RCT phase. If a participant’s psychological state deteriorates to a clinically significant degree during the trial, the investigators will discuss with the participant the possibility of withdrawing from the study, or may decide that the participant should be withdrawn. If withdrawn, participants will be referred to health care services as appropriate. Participants will also be informed that they can withdraw from the trial for any reason at any time without penalty. Should a participant withdraw or be withdrawn from the trial or be lost to follow up, relevant details will be documented. In the event of a physical or psychiatric emergency, participants will be advised to contact emergency services or visit the emergency department immediately. Participants incurring a physical injury as a result of participating in the trial will be eligible for compensation from Accident Compensation Corporation (ACC) under the Accident Compensation Act 2001 [142].

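### Infant outcomes are compared by actual exposure although both arms may take the multinutrients before birth, so the planned contrast is observational; within this exploratory aim, randomised arm should lead

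*Protocol article*

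**What the plan says.** The infant paragraph of Data analysis, whose stated purpose is to assess the effect of the intervention, says "we will compare those infants exposed to the multinutrients versus those infants not exposed to the multinutrients on emotional, cognitive and physical development". A continuous version follows, with the variation in exposure put down to two sources: "Length of exposure to the multinutrients (due to the RCT phase and varying starting points during gestation". The EPDS score is to be considered alongside it. The only adjustment named is for demographic differences between treatment groups. Earlier in the same section, all data are said to be analysed by intention to treat, whatever the compliance.

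Access to the multinutrients is described elsewhere:

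- Trial design: "The 12 week RCT phase of the trial will be followed by an open label phase where participants can take the multinutrient intervention". The reason given is the "opportunity to try the nutrients regardless of the random allocation in the RCT phase".
- Intervention: "all participants will be invited to enter an open label phase until the birth of their infants".
- Safety monitoring and reporting: the investigators "may decide to offer the open label option earlier if there is a worsening in symptoms during the RCT phase".
- Eligibility criteria: "Pregnant women who are between 12 and 24 weeks gestation will be recruited".

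The Aims section calls the infant part exploratory and asks whether length of exposure predicts temperament. Gestational age is among the birth outcomes collected (Infant measures).

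**The concern.** The open-label phase removes most of the group that the infant comparison relies on. A control mother's infant stays unexposed only if she declines open label, drops out, or delivers before her 12 weeks end. All three happen after randomisation and may be related to mood, health or the pregnancy. Early open label for worsening symptoms adds a route by which maternal depression causes exposure, while the same analysis treats the EPDS score as a predictor of infant outcome.

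Exposure length has a third source of variation that the plan does not name: the date of birth. Among women who continue, a shorter pregnancy means less exposure. An infant outcome that depends on gestation can then look like a response to supplementation. What is at stake is a self-selected contrast being reported as the effect of the intervention, when a randomised contrast is available from the same data.

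**Working it through.** **1. Exposure windows.** Inputs: entry at 12–24 weeks and a 12-week randomised phase (from the protocol); birth at 40 weeks (assumed).

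- Open label starts at 12 + 12 = 24 to 24 + 12 = 36 weeks.
- Control mother who accepts: 40 − 24 = 16 down to 40 − 36 = 4 weeks of exposure.
- Multinutrient-arm mother who continues: 40 − 12 = 28 down to 40 − 24 = 16 weeks.
- At any entry week the arms differ by 12 weeks. With birth at 37 weeks the ranges are 13 to 1 and 25 to 13.

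**2. Size of the unexposed group.** Inputs: 60 per arm and 30% attrition (Sample size). Open-label uptake *u* among control completers is not given, so 50–90% is assumed. Control dropouts: 0.30 × 60 = 18; completers: 42. Trial phase and follow up keeps those who discontinue in the postpartum assessments, so the dropouts count if they take no multinutrients.

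Unexposed = 42 × (1 − *u*) + 18

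| Uptake | Unexposed | Exposed (of 120) | Exposed who were randomised to control |
|---|---|---|---|
| 50% | 21 + 18 = 39 | 81 | 21/81 = 26% |
| 90% | 4 + 18 = 22 | 98 | 38/98 = 39% |

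**3. Precision.** The plan's own figure comes first: *n* = 2 × (1.960 + 0.842)² / 0.6² = 43.6, or 44 per group; the *t*-test version gives 44.6, or 45, as stated. That figure is for the maternal comparison; none is stated for infants. Using the same effect size only as a yardstick, power = Φ(0.6 × √(*n*₁*n*₂/(*n*₁ + *n*₂)) − 1.96):

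- 60 v 60 by arm: 0.6 × 5.477 − 1.96 = 1.33, power 0.91
- 81 v 39: 0.6 × 5.131 − 1.96 = 1.12, power 0.87
- 98 v 22: 0.6 × 4.239 − 1.96 = 0.58, power 0.72

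The loss of precision is moderate. The main issue is bias.

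**4. Exposure length.** With *B* the gestation at birth and *E* the gestation at entry, exposure is *B* − *E* for a continuing multinutrient-arm mother and *B* − *E* − 12 for an accepting control. *B* is therefore part of the exposure variable. Simulation with no treatment effect, all inputs assumed: entry uniform over 12–24 weeks, birth at mean 39.2 weeks (SD 1.8), 84–120 infants, uptake 50–90%. The exposure-length test is unadjusted at the 5% level:

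| Outcome–gestation correlation | False positives, exposure length | False positives, by arm |
|---|---|---|
| 0.10 | 5–6% | about 5% |
| 0.30 | 6–10% | about 5% |
| 0.55 | about 9–25% | about 5% |

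With birth SD 1.3–2.0 and uptake 70–90%, exposure length correlates 0.35–0.50 with gestation at birth among continuing multinutrient-arm mothers, and 0.11–0.24 over both arms, where the 12-week arm difference dilutes it. Its correlation with entry week is about −0.3 to −0.4.

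**5. Would exposure scheduled at entry help?** Scheduled exposure is 40 − *E* − 12 × (control). Once *E* is in the model, only the arm term is left, so this variable repeats the by-arm analysis.

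**The case against.** The infant aim is labelled exploratory. The primary outcomes are maternal, and no infant developmental measure is among the registered key secondary outcomes. This stands, and it limits how much the point matters.

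The intention-to-treat statement could be read as covering infants, and the infant paragraph does mention treatment groups and the randomised phase. It would therefore be too strong to infer that randomised arm plays no part. What stands is that a specific exposure-based rule follows a general statement it cannot be squared with, and no infant comparison by arm is described.

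A full covariate list is commonly left to an analysis plan, so not naming gestational age as an adjustment is not in itself a fault. The choice of contrast, however, is fixed in the article.

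The Aims section asks about length of exposure, which a by-arm comparison does not answer directly. That is fair, and it is a reason to keep the exposure analyses as secondary.

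A reader might also infer that the outcome determines the exposure. That holds only where gestational age is itself the outcome. Temperament, crying, bonding and social-emotional scores are measured after birth and cannot shorten exposure; for them the problem is confounding.

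**Conclusion.** The concern holds in a limited form. Exposed versus not exposed is a non-randomised contrast, because being unexposed depends on events after randomisation, and the intention-to-treat statement does not cure this. Exposure length is additionally confounded by gestational age at birth for outcomes related to gestation. Outcomes closely tied to gestation, such as birth weight, are the most exposed to this bias; for weakly related outcomes it is negligible.

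Two stronger readings are not supported. One is that the unexposed group is nearly empty: 4 to 21 infants remain only if the 18 control dropouts are set aside, and the protocol keeps following those who discontinue. The other is that about a third of null analyses would be significant: that needs a correlation of 0.55, complete uptake and no attrition, against the plan's own 30%. Uptake, the birth distribution and the outcome–gestation correlation are all assumptions, so the sizes are ranges. The maternal primary analysis is untouched.

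**What to change.** Reconcile the infant paragraph with the intention-to-treat statement:

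- Within the exploratory aim, make the leading infant analysis a comparison by randomised maternal arm, all infants as allocated. Describe it as about 12 weeks of earlier and longer exposure versus late or no exposure.
- Keep exposed/unexposed and realised exposure length as secondary analyses labelled observational, adjusted for baseline EPDS and gestation at entry.
- Add a sensitivity analysis adjusted for gestational age at birth, with the caveat that treatment may affect it, so the adjustment is not a full cure.
- Do not add a scheduled-exposure variable; after adjustment for entry gestation it only repeats the by-arm result.

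The cost is wording, since the variables are already collected. The downside is that the by-arm contrast does not estimate any versus no exposure.

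### Control variables for the infant analysis are picked by comparing randomised arms, while infants are compared by exposure, so selection into open-label use is picked up only by chance

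*Protocol article*

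**What the plan says.** All of the infant analysis stands in one paragraph of the Data analysis section.

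- The contrast: "we will compare those infants exposed to the multinutrients versus those infants not exposed to the multinutrients on emotional, cognitive and physical development".
- Continuous variables: "Length of exposure to the multinutrients (due to the RCT phase and varying starting points during gestation") is one. The same sentence adds that "score on the EPDS will also be considered as continuous variables in considering infant outcomes". A hierarchical regression then takes maternal depression and multinutrient exposure as predictors of infant self-regulation.
- The rule for control variables closes the paragraph: "Descriptive statistics for each participant will be used to compare demographic characteristics between the treatment groups to allow any differences to be controlled".

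The same section opens with another comparison: "Demographic characteristics will be compared across the treatment groups using independent samples" t-tests, given as a check on randomisation. There the treatment groups can only be the randomised arms.

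On who becomes exposed, the Intervention section says that after week 12 "all participants will be invited to enter an open label phase until the birth of their infants", and Trial design explains that this lets women try the nutrients whichever arm they were in. Safety monitoring and reporting adds that the investigators "may decide to offer the open label option earlier if there is a worsening in symptoms during the RCT phase".

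**The concern.** The grouping that is checked is not the grouping that is analysed. Women enter at 12 to 24 weeks, so the 12-week randomised phase ends at about 24 to 36 weeks (12 + 12 and 24 + 12), and most control women meet the open-label choice before birth. Exposed infants are then those of the multinutrient arm plus those of control women who took open-label capsules. Unexposed infants are mainly those of control women who did not. Choice forms that second group, and where open label is offered early, the mother's symptoms help to form it too.

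A maternal characteristic that drives uptake and also affects the infant will differ between exposed and unexposed. Randomisation makes its expected difference between arms zero, so a comparison by arm is not designed to show it. If the rule is followed as written, the effect of that characteristic can be read as an effect of the multinutrients.

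The rule also names demographics only. Smoking, alcohol, drug use and diet are measured (Maternal covariate outcome measures) and gestation at entry is known, but none of them is in the stated rule.

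**Working it through.** The plan gives no figure on this point, so there is none to reproduce. From the plan: 60 women per arm, 1:1 allocation, open label offered to all. Assumed: open-label uptake u among controls of 60-90%; a baseline variable U (mean 0, SD 1) that raises the odds of uptake by 1.5 to 3 per SD and correlates r = 0.2-0.3 with the infant outcome; no true effect of exposure; all infants analysed.

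**1. Group sizes.** Unexposed = 60 × (1 − u): 24 at 60%, 12 at 80%, 6 at 90%.

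**2. Imbalance by arm.** The expected value is 0 on any baseline variable, whatever drives uptake.

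**3. Imbalance by exposure.** Let D be the difference in U between control women who take open label and those who decline. Set decliners at 0 and takers at D. The multinutrient arm then has mean uD, and the exposed mean is (60·uD + 60u·D) / (60 + 60u), so

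exposed − unexposed = 2uD / (1 + u).

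D follows by numerical integration from the logistic uptake model, P(take) = 1 / (1 + exp(−(a + ln(OR)·U))), with a set so that uptake averages u. The bias in the infant contrast, in outcome SDs, is r times the imbalance.

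| u | OR | r | D | 2uD/(1+u) | Bias (SD) |
|---|---|---|---|---|---|
| 0.6 | 1.5 | 0.2 | 0.391 | 0.293 | 0.06 |
| 0.8 | 2 | 0.3 | 0.644 | 0.572 | 0.17 |
| 0.9 | 3 | 0.3 | 0.978 | 0.926 | 0.28 |

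Simulation of 60 per arm under the same assumptions agrees, and gives a bias of about zero once U is in the model.

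**4. How often the rule picks up U.** The SE of a standardised difference between arms is sqrt(1/60 + 1/60) = 0.183. A p<0.05 test flags U in 5% of trials by construction. A descriptive threshold of 0.2 SD gives z = 0.2/0.183 = 1.10, so about 27%; 0.1 SD gives z = 0.55, so about 58%. All of these are chance rates and do not rise with the strength of selection. In the middle setting, a p<0.05 comparison by exposure group flagged U in 47% of simulated trials.

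**5. Bias averaged over trials.** The table applies when U is not picked up. If U is adjusted for whenever flagged, the middle setting averages roughly 0.172 × 0.95 = 0.16 SD with the p<0.05 test and 0.172 × 0.73 = 0.13 SD with the 0.2 SD threshold.

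**6. A second set of assumptions.** With 45 per arm, uptake of 50-80%, D of 0.5 or 0.8 and an outcome slope of 0.5, the arm-based rule (p<0.05) gave a bias of 0.16-0.34 SD and a false-positive rate of 9-17%. Always adjusting gave about zero and 4-6%.

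**7. Scale.** The approximate SE of the unadjusted contrast is sqrt(1/96 + 1/24) = 0.23 at 60% uptake, sqrt(1/108 + 1/12) = 0.30 at 80% and sqrt(1/114 + 1/6) = 0.42 at 90%. In the three rows above, the bias is about a quarter (0.06/0.23), just over half (0.17/0.30) and two-thirds (0.28/0.42) of the SE.

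**The case against.** **The term may be loose.** The sentence stands in the infant paragraph, uses descriptive statistics instead of t-tests, and would largely repeat the earlier check if it also meant the arms. It might mean the groups just compared. That is possible, but the only clear use of the term in the section is for the randomised arms. If exposure groups were meant, the sentence still has to say so.

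**Part of the selection is modelled.** A reader might infer that differences due to open-label choice are never controlled. The article does not support that: EPDS score enters the infant analysis, and symptoms are a plausible driver of uptake. This stands, with two limits. The time point of the score is not fixed, and a score taken after exposure may be a mediator, not a confounder. Nor does EPDS stand in for smoking, alcohol, drug use, diet or gestation at entry.

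**No threshold is stated.** A reader might infer that a confounder almost always passes the check. That rests on a p<0.05 test that the article does not state; a looser descriptive rule flags more variables, though still by chance.

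**The arm check is not useless.** Infants are enrolled by separate invitation and 30% attrition is assumed, so arms among the infants analysed may differ by more than chance. The check should stay, but it is not enough.

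**The sizes are assumed and the aim is exploratory.** Both are true. The low end, 0.06 SD, is negligible, and the article does not define exposed. A full covariate list is commonly left to a SAP, so its absence is not the point. The point is that the rule the article does state uses the wrong grouping.

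**Conclusion.** The concern holds in a limited form. The infant contrast is by exposure and the rule for control variables is by randomised arm. Followed as written, the rule picks up determinants of open-label uptake only by chance (about 5% or 27% of trials under the two assumed thresholds). When such a variable is missed, the bias is about 0.06-0.28 SD under the assumed uptake, odds ratio and correlation; its sign depends on who declines. That the arm comparison is uninformative about selection does not depend on those assumptions, but the size of the bias does.

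The article does not support saying that selection goes wholly uncontrolled, or that the arms need no check. The infant aim is exploratory, which lowers the weight. The paragraph nevertheless sets out to assess an effect of the intervention on infant development, and the Aims attach a hypothesis to it, so the sentence is worth correcting.

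**What to change.** Replace the last sentence of the infant paragraph. For any exposed-versus-unexposed or length-of-exposure analysis of infants:

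- tabulate baseline characteristics by exposure group as well as by randomised arm;
- adjust for a short set fixed in advance from baseline data already collected, for example baseline EPDS, gestation at entry, smoking, and one socioeconomic or diet measure, instead of whatever differs between arms;
- report the result as an observational association, because unmeasured selection remains.

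The cost is one sentence and one table, with no new data collection. Adjustment may lose a little precision, and an unexposed group of about 6 to 24 infants (at 60-90% uptake) limits the number of covariates, so the set has to stay short.
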